##### Activity

Activity of vaccination will be measure by monitoring both clinical and immunologic parameters. The primary clinical parameter of activity will be PSA measurement. Secondary clinical parameters include monitoring of measurable disease, assessed by chest X-Ray, bone scan and CT scan/MRI scans.

PSA will be measured in the MSKCC laboratory and serially monitored starting at the screening visit, Day 0, Week 3, 4, 5, 7, 9, 13, and 17, (and possibly 29) for participants in Arm 1 and on screening visit, Week 3, 4, 5, 6, 7, 9, 11, 12, 13, 15, 17, 21, and 25, (and possibly 37) for participants in Arm 2.

Complete response (CR): PSA < 4.0 ng/ml for 3 successive evaluations at least two weeks apart.

Partial Response (PR): Decrease in PSA value by > 50% (without normalization) for three successive evaluations at least two weeks apart.

Stabilization (SD): Patients who do not meet the criteria for PR or PD for at least 90 days on study (post vaccine; week 1 (Arm 1) or week 10 (Arm 2)).

Progression (PD): Three consecutive increase in PSA from baseline or nadir, each measurement at least two weeks apart.

Time to PSA Progression: The first PSA rise after the nadir PSA that is confirmed by two consecutive PSA at least two weeks or more apart.

Measurable disease

Patients will be evaluated at baseline, and at 5 weeks and 17 weeks after completion of therapy. Response and progression of measurable disease will be evaluated by bone scan and soft-tissue CT scan, using criteria proposed by the Response Evaluation Criteria in Solid Tumors (RECIST) Committee (Therasse et al., 2000). Changes in only the largest diameter (uni-dimensional measurement) of the tumor lesions are used in the RECIST criteria. Note: Lesions are either measurable or non-measurable using the criteria provided below.

Measurable disease: Defined as lesions that can be accurately measured in at least one dimension (longest diameter to be recorded) as >20 mm with conventional techniques (PET, CT, MRI, x-ray) or as >10 mm with spiral CT scan.

Non-measurable disease: All other lesions, including small lesions, are considered non-measurable disease. Bone lesions, leptomeningeal disease, ascites, plueral/pericardial effusions, lymphangitic disease, inflammatory disease are all non-measurable.

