Target lesions: All measurable lesions up to a maximum of five per organ and 10 in total representative of all involved organs should be identified as target lesions and recorded and measured at baseline. Target lesions should be selected on the basis of their size (lesions with the longest diameter) and their suitability for accurate repeated measurements (either by imaging techniques or clinically). A sum of the longest diameter (LD) for all target lesions will be calculated and reported as the baseline sum LD, which will serve as a reference by which to characterize tumor response.

Non-target lesions: All other lesions should be identified as non-target lesions and should also be recorded at baseline. Non-target lesions include measurable lesions that exceed the maximum numbers per organ or total of all involved organs as well as non-measurable lesions. Measurements of these lesions are not required, but the presence or absence of each should be noted throughout follow-up.

Guidelines for evaluation of measurable disease: All measurements should be taken and recorded in metric notation using a ruler or calipers. All baseline evaluations should be performed as closely as possible to the beginning of treatment and never more than 4 weeks before the beginning of the treatment. Tumor lesions that are situated in a previously irradiated area are not considered measurable. The same method of assessment and the same technique should be used to characterize each identified and reported lesion at baseline and during follow-up. Imaging-based evaluation is preferred to evaluation by clinical examination when both methods have been used to assess the antitumor effect of a treatment.

Radionuclide bone scan

Subjectivity in interpreting serial changes in radionuclide bone scan is well recognized. Thus the primary outcome will be whether the scan is stable or improved, vs. worse or progression. Changes in intensity will not be used as an outcome measure.

Stable or improved: Requires that no new lesions appear, or that new pain has not developed in an area that was previously visualized.

Progression (Non-response): New areas of focal uptake.

Time to Progression: Time to progression will be defined as the time from the first day of treatment with vaccine until the date PD or death is first reported. Patients who die without a reported prior progression will be considered to have progressed on the day of their death.

Chest x-ray

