#### Biostatistical analysis.

The primary specific aim is to compare the clinical status during the first part of the study (before the cross-over) between the placebo and the vaccine group. As defined in CFR, Phase-I/II studies should address both acute toxicity and activity/efficacy. Accordingly, this comparison will be based on two primary outcomes:

(1) activity: relative change in PSA.

We do not use the term “efficacy” here, because we recognize that change in PSA is not a validated “surrogate” for clinical benefit. The primary manifestations of disease progression in prostate cancer are rising PSA values, new lesions on bone scan, new symptoms of disease, and, less frequently, an increase in measurable tumor mass. Several groups have shown the prognostic significance of post-therapy declines in PSA, leading to an NCI consensus group proposal of a set of guidelines for the use of post-therapy PSA that can be used in phase II trials to identify agents for further testing (Fazzari et al., 2000).

(2) acute toxicity: incidence and severity of an adverse events.

Although the variables will be combined to address the overall clinical status, the power calculations below address each of these aspects independently.

Size of relevant differences: For activity, we would like to have sufficient power to detect a 50% decline in PSA in the treatment group vs. no change in the placebo group. For toxicity, we would like to have sufficient power to detect a 50% incidence of severe adverse events (acute toxicity) vs. a 5% incidence.

Power vs. level: If there should be acute toxicity, we do not want to overlook this (false negative result). A similar argument holds for activity: as long as the treatment with apoptotic LNCaP-DCs is well tolerated, we would rather go on with the next trial, even if we would later find out that apoptotic LNCaP-DCs are not active (false positive result), than to risk delaying the development of an effective treatment (false negative result). Thus, we want to guarantee 90% power for the above differences at the 10% level. If we should see lower acute toxicity in the vaccine group (unlikely) or higher activity in the placebo group (also unlikely), our decision would be the same as if we would see no difference: we would reconsider the use of this vaccination in the treatment of advanced prostate cancer. Given this one-sided decision strategy we will further increase power by using one-sided tests.

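### PSA progression has no minimum rise and an ambiguous confirmation rule, so false progression in a man with unchanged PSA is about 10% or up to 76%, depending on how the text is read

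*Combined protocol and SAP*

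**What the plan says.** All the PSA definitions stand in the combined protocol and SAP under (6)i.h Outcome Parameters, Activity.

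- The line that dates PSA progression, for the time-to-event outcome: "The first PSA rise after the nadir PSA that is confirmed by two consecutive PSA at least two weeks or more apart".
- The line that sets the PD category requires, in its words: "Three consecutive increase in PSA from baseline or nadir, each measurement at least two weeks apart".
- PR (partial response) is given as: "Decrease in PSA value by > 50% (without normalization) for three successive evaluations at least two weeks apart".
- Stable disease (SD), defined by exclusion: "Patients who do not meet the criteria for PR or PD for at least 90 days on study".
- PSA sampling after screening, first arm: "Day 0, Week 3, 4, 5, 7, 9, 13, and 17, (and possibly 29) for participants in Arm 1".
- The corresponding list for the second arm, which spans placebo and crossover: "Week 3, 4, 5, 6, 7, 9, 11, 12, 13, 15, 17, 21, and 25, (and possibly 37").

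The same section has a general time to progression, placed under the bone-scan criteria, that runs "until the date PD or death is first reported". No percentage or ng/ml minimum for a PSA rise appears in these lines or elsewhere in the documents. The text also does not say whether the nadir is the lowest value so far (running) or the lowest over the whole follow-up (final).

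Under (6)i.n Data analysis, Biostatistical analysis, the primary activity outcome is "1) activity: relative change in PSA", tested by Wilcoxon-Mann-Whitney.

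**The concern.** A nadir is the lowest value, so apart from ties every later value is above it, by however little. If the confirming values need only exceed the nadir, the rule mainly asks whether enough visits remain after the lowest value. If instead each value must exceed the one before, the rule is much stricter, and a single noisy dip breaks the sequence in a man whose PSA is truly rising. The text supports both readings.

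Two analysts following the text could therefore classify the same men very differently as PD or SD and give them different progression dates. Nothing says which category prevails when a man meets both PR and the progression rule.

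**Working it through.** **Inputs.** Values at least two weeks apart: Arm 1 at weeks 0, 3, 5, 7, 9, 13 and 17; Arm 2 from crossover at weeks 9, 11, 13, 15, 17, 21 and 25. That is seven per man, including the pre-vaccination value (eight with the optional late visit). There are 12 men per arm. The documents give no progression rate to reproduce, and no assay or biological coefficient of variation (CV); CVs below are assumptions. I take a first rise plus two confirming values as three values in all.

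**Unchanged PSA, values need only exceed the nadir.** With independent noise and no ties only the ranking matters, so the result does not depend on the CV.

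- Final nadir: the lowest of seven is equally likely at each position, and three later values exist for positions 1 to 4. Probability = 4/7 = 57.1%.
- Running nadir: let r(k) be the chance that no earlier run of three values above the running nadir has occurred, given that the lowest value so far is at position k. Then r(1) to r(4) = 1, and r(k) = [r(k−1) + r(k−2) + r(k−3)]/(k−1). So r(5) = 3/4 = 0.75, r(6) = 2.75/5 = 0.55 and r(7) = 2.30/6 = 0.383. The rule fails to fire only if the final nadir is at position 5, 6 or 7: (0.75 + 0.55 + 0.383)/7 = 0.240. Probability of firing = 76.0%. Enumerating all 7! orderings agrees.

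**Unchanged PSA, three successive increases.**

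- From the final nadir: (4/7) × (1/3!) = 4/42 = 9.5%.
- By enumeration: 12.7% from baseline or running nadir, 14.2% from any point.

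**Per 12 men with unchanged PSA.** 12 × 0.571 to 12 × 0.760 = about 7 to 9 false progressions on the first reading; 12 × 0.095 to 12 × 0.142 = about 1 to 2 on the second.

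**Partial responders who plateau** (Arm 1 schedule, simulated; plateau at 30–40% of baseline and CV 10–20% assumed):

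| Plateau from week | Above nadir, final | Above nadir, running | Three successive increases |
|---|---|---|---|
| 3 | 50% | 62% | 10% |
| 5 | 40% | 45% | 8% |
| 7 | 25% | 25% | 4% |

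The final-nadir column is again simple counting: 3/6, 2/5 and 1/4.

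**One man in two categories.** Take PSA 20, 12, 6.0, 6.1, 6.1, 6.2, 6.1. Half of baseline is 10, and the last five values are below it without falling under 4.0, so PR is met. The values after 6.0 all exceed it, so the above-nadir rule is met too. Three successive increases are not met, because 6.1 to 6.1 is a tie.

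**True slow riser** (26-week doubling time, CV 10%, both assumed), called by week 17: about 99% above the running nadir; about 34% with three successive increases from baseline or nadir.

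**With a minimum rise** above the running nadir on all three values, unchanged PSA:

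| Minimum rise | CV 5% | CV 10% | CV 15% | CV 20% |
|---|---|---|---|---|
| none | 76% | 76% | 76% | 76% |
| 10% | 8% | 34% | 47% | 55% |
| 25% | <0.1% | 4% | 16% | 27% |
| 50% | 0% | <0.1% | 1.3% | 5.8% |

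At a 25% minimum, plateaued responders are called progressed in 0.5–2.5% (CV 10%) or 5–19% (CV 20%). The slow riser above is called in about 62% by week 17.

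**The case against.** The strongest reply is that the PD line sets the category, and its ordinary meaning is three successive increases. The time-to-progression line can be read as only dating that event. False progression is then about 10–14%. This stands as a plausible reading, and a reader who infers that most men with unchanged PSA will be called progressed goes beyond the documents. But the text does not settle the point, and the stricter reading misses many slow risers.

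Second, men enter with rising PSA, so an unchanged PSA is not the expected course, and real noise may be serially correlated. That stands as a limit on the rates. Rounding also matters: reporting to 0.1 ng/ml (CV 10%) lowers 76% to 64% at PSA 2 and 71% at PSA 5. Yet the sample-size section supposes falling PSA in two-thirds of vaccinated men, so falls and plateaus are part of the plan's own active scenario.

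Third, progression after a response is legitimate, and counting from the nadir anticipates it. True, but a genuine relapse should be distinguishable from a plateau, and without a minimum rise it is not.

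Fourth, the primary test does not use these categories. That is correct and limits the consequence.

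**Conclusion.** The point holds as a missing minimum rise combined with an undefined comparator for the confirming values. With unchanged PSA, false progression is 57–76% or about 10–14% according to the reading; for plateaued partial responders it is about 25–62% or 4–10%. These figures assume independent noise and seven usable values; the plateau figures also assume the levels and CVs stated.

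It affects PD, SD and time to PSA progression, and the general time to progression if its PD includes PSA progression. These are secondary and descriptive. The Wilcoxon comparison and the combined benefit score use relative PSA change and are untouched, so the documents do not support a claim that the primary activity conclusion is at risk.

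Three other inferences also fail:

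- That progression would reflect noise and not treatment. Even on the above-nadir reading with a running nadir, the rule fires in 99% of slow risers, 76% of unchanged men, 45% of responders who plateau from week 5, and 3% of steady fallers (halving over 17 weeks, CV 10%, assumed). It is noisy but informative.
- That deeper responses are penalised. Timing of the plateau matters; depth does not.
- That few men would remain stable. SD is judged at 90 days, and 90/7 = 12.9 weeks. By week 13 (six values) false progression is 50–62% or 8–11%, which leaves 38–50% or about 90% of unchanged men not progressed.

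**What to change.** Use one definition of PSA progression for PD, SD and time to PSA progression:

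- a pre-stated minimum percentage rise above the running nadir, or above baseline if there was no fall, chosen to exceed assay variation;
- confirming values at least two weeks apart that are also above that threshold;
- dated at the first value that crosses it;
- a statement that a man in PR is not PD until the threshold is crossed.

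The 25% used above is an illustration, not a figure from the documents. The choice should rest on the laboratory's own PSA variation, because at a CV of 15–20% a 25% minimum still gives 16–27% false progression in unchanged men.

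The change is to text only and needs no new samples or visits; it should be made before the PSA outcomes are analysed. The cost is later calls for slow risers than under the above-nadir reading: about 62% against 99% by week 17 (26-week doubling, assumed CV 10%), in exchange for 4% against 76% false progression. At that CV the 25% rule does better than three successive increases from baseline or nadir on both counts: 62% against about 34% of slow risers called, and 4% against about 13% of unchanged men.

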#### Duration

Immunizations will be given over the course of 7 weeks. All patients will be followed to Week 17 (Arm 1) or Week 25 (Arm 2). The longest duration of follow-up will be blood draws 29 (Arm 1) or 37 (Arm 2) weeks after study entry in selected patients with either clinical or immunological responses or adverse events. Patients who have completed at least 13 weeks (Arm 1) or 21 weeks (Arm 2) of the study will be considered to have completed the study, although all patients will be encouraged to remain in the study for the full 17 (Arm 1) or 25 (Arm 2) weeks.

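### On the all-patient PSA schedule, a rise first seen after week 9 (Arm 1) or week 17 (Arm 2) cannot get two confirming values, so a late riser can meet the definition of stabilization

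*Combined protocol and SAP*

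**What the plan says.** All of this is in the combined protocol and SAP.

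- **Progression (Activity):** "Three consecutive increase in PSA from baseline or nadir, each measurement at least two weeks apart".
- **Time to PSA progression (Activity):** "The first PSA rise after the nadir PSA that is confirmed by two consecutive PSA at least two weeks or more apart". No time origin, censoring rule or analysis method is given for it.
- **Stabilization (Activity):** "Patients who do not meet the criteria for PR or PD for at least 90 days on study", counted from week 1 in Arm 1 and week 10 in Arm 2.
- **CR and PR (Activity):** each needs three successive evaluations at least two weeks apart.
- **PSA visits (Activity):** screening, Day 0 and "Week 3, 4, 5, 7, 9, 13, and 17, (and possibly 29) for participants in Arm 1". The Arm 2 list ends "17, 21, and 25, (and possibly 37) for participants in Arm 2".
- **Follow-up (Duration):** every patient is followed to week 17 or week 25. The week 29/37 blood draw is taken "in selected patients with either clinical or immunological responses or adverse events".
- **Completion (Duration):** a man who reaches week 13 in Arm 1, or week 21 in Arm 2, already counts as a completer.
- **Primary activity outcome (Biostatistical analysis):** relative change in PSA before the cross-over, compared by a Wilcoxon-Mann-Whitney test.

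**The concern.** A confirmed endpoint needs visits left over in which to confirm it. Here the PSA visits thin out to two per arm just as confirmation requires two more values, and no rule covers a rise that is still unconfirmed when the schedule ends. The SD definition then takes in these men by default, because it asks only that PR and PD were not met.

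The extra draw at week 29/37 does not repair this evenly. A late response is itself a ground for the draw. A late progression is not, so a late progressor gets it only if he was selected for some other reason.

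At stake are the post-vaccine PSA categories and time to PSA progression. From week 9 both arms are on or past vaccine, so these summaries have no concurrent placebo to be read against. A PSA effect that fades after the fourth dose could appear in the report as stability.

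**Working it through.** **Inputs.** PSA visits, PD, SD and time-to-progression rules: Activity. First vaccine at week 1 (Arm 1) and week 9 (Arm 2): Dosing Plan. Last all-patient visit and completion rule: Duration. The plan states no figure for PSA progression, so there is none to reproduce.

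**Step 1: which first rises can be confirmed.** For each visit, look for the required number of later PSA values, each at least two weeks after the one before.

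| Visits available | Values needed after the first rise | Last countable first rise, Arm 1 / Arm 2 | Weeks after first vaccine |
|---|---|---|---|
| All-patient schedule | 2 | 9 (then 13, 17) / 17 (then 21, 25) | 8 |
| All-patient schedule | 1 | 13 (then 17) / 21 (then 25) | 12 |
| With the optional week 29/37 draw | 2 | 13 (then 17, 29) / 21 (then 25, 37) | 12 |
| Leaves at week 13/21 | 2 | 7 (then 9, 13) / 15 (then 17, 21) | 6 |

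Weeks after first vaccine: 9 − 1 = 8 and 17 − 9 = 8; the other rows follow in the same way.

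**Step 2: who then meets SD.** Ninety days from week 1 is 1 + 90/7 = week 13.9. Ninety days from week 10 is 10 + 90/7 = week 22.9.

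- Followed to week 17: (17 − 1) × 7 = 112 days. Followed to week 25: (25 − 10) × 7 = 105 days. Both pass 90, so an unconfirmed riser without CR or PR is SD.
- Leaves at week 13: (13 − 1) × 7 = 84 days. Leaves at week 21: (21 − 10) × 7 = 77 days. Neither reaches 90, so such a man cannot be SD. If his rise is unconfirmed he is not PD either, and he has no category.

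**Step 3: an invented example in Arm 1.** PSA is 10 at Day 0, does not rise up to week 9, and is 8 at week 9, 16 at week 13 and 32 at week 17. There are two increases, so PD is not met if three are needed. The fall from 10 to 8 is 20%, so PR is not met. At day 112 he is SD, with PSA at 32/8 = 4 times nadir. If PD means three rising values, 8-16-32 qualifies and he is PD.

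**Step 4: illustrative size.** Assume that time from first vaccine to first rise is exponential, S(t) = 2^(−t/median), with full follow-up, censoring at the last PSA and no optional draw. Of progressions beginning within 16 weeks, the share that cannot be counted is (S(c) − S(16)) / (1 − S(16)), with c = 8 if two later values are needed and c = 12 if one is.

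| Assumed median (weeks) | S(8) | S(12) | S(16) | Lost, two later values | Lost, one later value |
|---|---|---|---|---|---|
| 2 | 0.063 | 0.016 | 0.004 | 6% | 1% |
| 4 | 0.250 | 0.125 | 0.063 | 20% | 7% |
| 8 | 0.500 | 0.354 | 0.250 | 33% | 14% |
| 12 | 0.630 | 0.500 | 0.397 | 39% | 17% |
| 24 | 0.794 | 0.707 | 0.630 | 44% | 21% |

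**The case against.** Several points on the other side are sound and limit the finding.

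- **The PD wording is loose.** The entry criteria count three rising values, not three increases, and after radiation take the first of the three as baseline. On that convention a first rise at week 13/21 is confirmed at week 17/25, and only first rises at week 17/25 are missed. The definition of time to PSA progression can likewise be read with the first rise as one of its two values. The text does not settle either reading.
- **The optional draw can confirm progression too.** A reader might infer that a late rise can never be counted. That goes too far: weeks 13-17-29 or 21-25-37 confirm it, and a man selected as a responder whose effect then fades is among those who may be drawn. What stands is that selection depends on outcome and that progression is not a ground for it.
- **Dating is not fixed.** A reader might infer a curve that is flat by construction after 8 weeks. That needs timing from first vaccine, dating at the first rise, two later values, and a censoring rule that the plan does not contain. The general time to progression, under the bone scan heading, runs to the date PD is first reported, which could be as late as week 17/25, 16 weeks after first vaccine.
- **No comparison is biased.** A reader might infer a tilt towards vaccine over placebo. Both arms are vaccinated, the cut-off is 8 weeks after first vaccine in both, and no between-arm test or survival analysis of these endpoints is planned.
- **The medians are assumptions.** All patients enter with rising PSA, so short times to first rise are plausible, and these give the smaller losses.
- **The record is incomplete.** The schedule-of-events table is not visible in the text available, and other sections mention follow-up to 41 weeks against the 29/37 weeks under Duration. Those sections need reconciling.

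Some loss at the end of follow-up comes with any confirmed endpoint. That does not justify calling the affected men stable.

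**Conclusion.** The concern holds in limited form. On the all-patient schedule, with two later values required, the last countable first rise is week 9 in Arm 1 and week 17 in Arm 2. A later riser without CR or PR who stays to week 17/25 meets SD as written, and one who leaves at week 13/21 has no category. If three rising values are enough, the gap narrows to first rises at week 17/25. Late ascertainment through week 29/37 depends on outcome under either reading.

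The effect is confined to the descriptive post-vaccine PSA categories and time to PSA progression. The primary pre-cross-over PSA comparison and the sample size do not depend on it. The documents support no single size: the losses of about 6% to 44% (two later values) rest on the exponential model, the censoring rule and the assumed medians of 2 to 24 weeks. The definitions should be corrected before these summaries are reported.

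**What to change.** Change the PSA definitions in the Activity section.

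1. State whether PD needs three increases or three rising values, and use the same confirmation rule for PD and for time to PSA progression.
2. Report a man whose last values are successive rises from nadir, with no scheduled visit left to confirm them, as unconfirmed progression, separate from SD. This also gives a category to such men who leave at week 13/21.
3. For time to PSA progression, CR and PR, set one last-confirmable visit from the all-patient schedule and apply it to everyone, including patients who have a week 29/37 draw. When two later values are needed, it is week 9/17 with full follow-up and week 7/15 for a man who leaves at week 13/21. Report events or responses confirmed only by the week 29/37 PSA separately, so that selective draws alter neither the response rates nor time to progression.

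Cost: no added visits or patients. The SD rate will look less favourable, and time to PSA progression will cover a shorter window.

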#### Dosing Plan

All prostate cancer patients will undergo two leukapheresis procedures, one prior to vaccination and a second 6 weeks after the final vaccination. Those in Arm 2 will undergo a third leukaphereesis, prior to the placebo phase. Their cells will be cryopreserved in aliquots and will serve as a source of (prevaccination or postvaccination) cells throughout the study and will reduce the number and volume of blood draws.

The study is divided into 2 Arms of 12 patients each.

Arm 1 will have autologous DCs generated from pre-vaccination leukapheresis cells. Laboratory manipulation of the cells will be done according to Good Laboratory Practice guidelines. Cells will be co-cultured with apoptotic LNCaP or LNCaP-M1 tumor cells for an average of 36 hours (range 30-48 hours) prior to immunization. Vaccinations will occur on weeks 1, 3, 5 and 7. On weeks 1 and 3 patients will also be immunized with mature DCs exposed to KLH. For each subject, the maximal number of available DC will be re-injected with an anticipated range of 2 x 106 to 10 x 106 cells, depending on cell availability, in 0.5 ml volume. Patients will also be injected with either saline or vaccine vehicle only (5% DMSOin normal saline) at weeks 1, 3, 5 and7.

Arm 2 will have placebo (either saline or vaccine vehicle only (5% DMSOin normal saline )) injected on week 1, 3, 5 and 7, and will then switch over to DC/LNCaP and DC/LNCaP-M1 immunization on weeks 9, 11, 13 and 15. On weeks 9 and 11 patients will also be immunized with mature DCs exposed to KLH. Patients will also be injected with either saline or vaccine vehicle only (5% DMSO in normal saline ) at weeks 9, 11, 13 and15.

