### Stopping rules

#### Criteria for Subject Study Discontinuation

- Development of an exclusionary condition as outlined in section (6)i.e.2, prior to or during vaccination, with the following exceptions:
  - a course of palliative radiation treatment during the study
- platelet counts that drop > 50% from baseline.
  - hemoglobin that drops sufficiently to require transfusion.
  - if the patient develops an infection requiring treatment as an inpatient.
- Failure by the subject to attend three consecutive clinical study visits.
- Request by the subject to withdraw.
- Clinical reasons judged by the study physician to be life threatening, even if not addressed in the toxicity management of the protocol.
- Completion of week 17 or in some patients, week 29 in Arm 1.
- Completion of week 25 or in some patients week 37 in Arm 2.
- Any dose limiting toxicity. A dose limiting toxicity is defined as:
  1. any grade 2 or greater allergic toxicity or asymptomatic bronchospasm or generalized urticiaria
  2. any grade 3 or greater toxicity (hematologic or non-hematologic)
  3. any grade 2 or greater autoimmune reactions

If a subject discontinues prior to completion of the study, the reason for and date of the discontinuation will be recorded. The date of the last dose of study vaccine will also be recorded. Subjects who discontinue prior to study completion may be replaced at the discretion of the Investigator.

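### The second measurable-disease evaluation falls at week 24 (Arm 1) or 32 (Arm 2), seven weeks after follow-up of all patients ends; separately, early completers cannot be classed for 90-day stabilization

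*Combined protocol and SAP*

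**What the plan says.** **Imaging.** Under Activity, measurable disease is a secondary clinical parameter: "Patients will be evaluated at baseline, and at 5 weeks and 17 weeks after completion of therapy". The Dosing Plan fixes when therapy ends. For Arm 1, "Vaccinations will occur on weeks 1, 3, 5 and 7". Arm 2, after placebo, "will then switch over to DC/LNCaP and DC/LNCaP-M1 immunization on weeks 9, 11, 13 and 15".

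**Follow-up.** The Duration section states: "All patients will be followed to Week 17 (Arm 1) or Week 25 (Arm 2"). Beyond that, "The longest duration of follow-up will be blood draws 29 (Arm 1) or 37 (Arm 2) weeks after study entry in selected patients", these being patients with responses or adverse events. The Criteria for Subject Study Discontinuation list "Completion of week 17 or in some patients, week 29 in Arm 1" as an exit point, with weeks 25 and 37 for Arm 2. Monitoring and follow-up gives the later visits as weeks 9, 13, 17 and possibly 29 (Arm 1) and weeks 17, 21, 25 and possibly 37 (Arm 2).

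**Other statements on length.** Planned Duration puts the longest follow-up at 41 weeks after entry. Indications to be studied asks for availability of up to 41 weeks from screening, and Subjects asks for at least 41 weeks.

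**Stabilization.** The PSA criteria require no PR or PD "for at least 90 days on study (post vaccine; week 1 (Arm 1) or week 10 (Arm 2")). Yet the Duration section says that a patient who has "completed at least 13 weeks (Arm 1) or 21 weeks (Arm 2) of the study will be considered to have completed the study", while encouraging everyone to stay to week 17 or 25.

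**The concern.** An endpoint reading set for a time after patients have left the study cannot be collected as intended. If the second evaluation is done only in patients kept on to week 29 or 37, it comes from men selected for a response or an adverse event, and any summary of measurable disease at that point describes a selected group. Time to progression, which depends partly on these scans, is affected in the same way.

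Stabilization raises a smaller question of the same kind. The protocol lets a patient count as having completed the study before the 90 days have run, and gives no rule for placing him if he has had no CR, PR or PD. The stabilization clock also starts at the first vaccination in Arm 1 but one week after the first active vaccination in Arm 2.

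**Working it through.** **1. Check the calendar against the plan's own visits.** Visit week = last vaccination week + stated offset. The DTH offsets (2, 10 and, in some patients, 22 weeks; Immunologic Studies) and the leukapheresis offset (6 weeks; Dosing Plan) give:

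- Arm 1: 7 + 2, 6, 10, 22 = weeks 9, 13, 17, 29.
- Arm 2: 15 + 2, 6, 10, 22 = weeks 17, 21, 25, 37.

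Both lists match Monitoring and follow-up exactly, so weeks can be counted from the last vaccination.

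**2. Apply the same rule to imaging (offsets 5 and 17 weeks).**

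| | First | Second | All-patient follow-up ends | Second scan minus end |
|---|---|---|---|---|
| Arm 1 | 7 + 5 = 12 | 7 + 17 = 24 | 17 | 7 weeks = 49 days |
| Arm 2 | 15 + 5 = 20 | 15 + 17 = 32 | 25 | 7 weeks = 49 days |

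The imaging window is 10 days (Definitions for Schedule of Events). The first scan is 7 days from the week 13 or 21 visit, so it fits. The second is still 49 − 10 = 39 days beyond week 17 or 25, and it is 5 × 7 = 35 days before week 29 or 37. It fits no listed follow-up visit. Reading completion of therapy as week 8 or 16 moves the second scan later, to week 25 or 33.

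**3. Stabilization days = 7 × (end week − start week).**

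| Leaves at | Arm 1, from week 1 | Arm 2, from week 10 (as stated) | Arm 2, from week 9 (first active vaccination) |
|---|---|---|---|
| Completion minimum (week 13 / 21) | 84 | 77 | 84 |
| Full follow-up (week 17 / 25) | 112 | 105 | 112 |

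Ninety days are reached at 1 + 90/7 = week 13.9 (Arm 1). In Arm 2 they are reached at 10 + 90/7 = week 22.9, or at week 21.9 if counted from week 9. The first scheduled PSA that satisfies the rule is therefore week 17 (Arm 1) or week 25 (Arm 2) on either clock. The minimum completer is 6 days short in Arm 1, and 13 days (from week 10) or 6 days (from week 9) short in Arm 2. Arm 2 has no PSA listed at week 10.

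Counting from leukapheresis, 8 days before the first vaccination, would give 84 + 8 = 92 days, but the criterion is written as post vaccine.

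**The case against.** **The 41-week statements.** Weeks 24 and 32 lie inside 41 weeks, so follow-up might be said to cover the second scan. That is a fair reason not to claim that the scan will certainly be missed. But those passages give a maximum and an availability requirement, and they schedule no visit. They conflict with the Duration section, the discontinuation criteria and the visit list. They therefore add a contradiction.

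**The Schedule of Events.** Imaging dates are tied to Table 2, whose contents are not legible in the copy reviewed. It may place the scans elsewhere, so what would happen in practice cannot be judged. The conflict between the text sections stands whatever the table shows.

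**Stabilization.** A reader might infer that follow-up ends before stabilization can be read at all. The documents do not support this. All patients are to be followed to week 17 or 25, PSA is scheduled there, and 112 or 105 days exceed 90. Patients are encouraged to stay, and those who withdraw are asked to continue in follow-up. Only the patient who leaves at the completion minimum is affected.

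**Impact.** A reader might also infer bias in the arm comparison. The primary comparison is relative PSA change and toxicity before cross-over, and the Data analysis section plans no between-arm test of stabilization or of measurable-disease response. Eligibility rests on rising PSA and CT/MRI is for indicated patients, so some men may have no measurable lesion. These points stand and limit the severity.

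**Conclusion.** The imaging conflict holds: in both arms the second measurable-disease evaluation is 49 days after follow-up of all patients ends, or 39 days using the whole imaging window. On the text of the Duration section and the discontinuation criteria, it is obtained in no one or only in patients selected by outcome. This assumes that completion of therapy means the last vaccination; a later reading widens the gap. The 41-week statements leave the intended length of follow-up unresolved.

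For stabilization, the finding is limited to early leavers: 84 days, or 77 on Arm 2's stated clock, against 90, with no rule for classifying them. The week 10 versus week 9 start is a genuine inconsistency between arms, but it does not change which scheduled visit first satisfies the criterion.

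Sample size, power and the primary analysis are unaffected. Severity: minor.

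**What to change.** 1. **Imaging and length of follow-up.** Reconcile Planned Duration, Indications to be studied, Subjects, Duration, Activity, Monitoring and follow-up, and the discontinuation criteria, and check Table 2 against the result. The second evaluation should fall at a visit all patients have.
   - The lowest-cost option is the existing week 17 / 25 visit. It needs no added visit. The price is a reading 10 weeks after the last vaccination instead of 17, and only 17 − 12 = 25 − 20 = 5 weeks after the first scan.
   - If the 17-week reading is to be kept, state that follow-up covers week 24 / 32 for everyone. That means 7 more weeks of follow-up and one further visit per patient, up to 24 visits.
2. **Arm 2 clock.** Start the stabilization clock at the first active vaccination, week 9, as Arm 1 starts at week 1. This is a wording change only.
3. **Stabilization.** Keep the 90-day criterion and name week 17 / 25 as the point at which it is evaluable. Report patients who leave earlier without PR or PD as not evaluable for stabilization, and give their number by arm. The cost is a smaller evaluable group if some patients leave at week 13 / 21.
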